## Abstract

**Background:**

The number of patients with one or more chronic diseases is rising. In several standards of care there is a focus on enhancing self-management. We applied the concept of personalization on self-management support and developed a self-management screening questionnaire (SeMaS). The main research objective is to assess the effectiveness of the SeMaS questionnaire and subsequent personalized self-management on patients’ self-management behaviors.

**Methods/Design:**

A cluster randomized controlled trial will be set up in 15 general practices in the Netherlands. The practices are all group practices, and member of one care group. The practices will be assigned to the control or intervention arms by stratified randomization. The strata are determined by the participation of the practice nurses in a course for behavioral change, and the nurse’s workload. Patients can be included if they are over 18 years of age, have at least one chronic condition and have a checkup appointment with the practice nurse in the inclusion period. The intervention consists of screening patients with the SeMaS questionnaire, producing a graphic profile with the abilities or barriers for self-management. Patients will receive tailored feedback. Practice nurses are trained in using the profile to enhance self-management of the patient and provide personalized self-management support. The use of individual care plans and self-management interventions is stimulated. In the control arm patients will receive care as usual. Patients of both trial arms will be asked to fill in the SeMaS questionnaire and additional questionnaires at inclusion and after 6 months. The primary outcome is the difference in the level of patient activation (PAM-13) between baseline and 6 months. Secondary outcomes include patient measures for lifestyle factors (exercise, diet, smoking), and process measures from medical record data analysis.

**Discussion:**

This manuscript presents the protocol for a cluster randomized clinical trial of personalized self-management support using the SeMaS questionnaire in chronically ill patients in primary care. By carrying out this study, scientific evidence is built for the effectiveness of personalized self-management support.

**Trial registration:**

The Netherlands National Trial Register: NTR3960.

## Background

The number of patients with one or more chronic conditions is vastly rising worldwide. In the United States, 133 million people suffered from one or more chronic disease in 2005 [1]. Hoeymans *et al*. stated that in the Dutch population 4.5 million people (28%) suffer from at least one chronic disease [2]. Tacken *et al*. showed that the percentage of patients who suffered from at least one chronic disease rose from 12.6% in 2003 to 15.0% in 2009 [3]. This can be explained by ageing of the population. The increase in number of patients with one or more chronic diseases will increase the workload in primary care, and increase healthcare costs. Chronically ill patients usually have several consultations with their general practitioner (GP) or practice nurse each year.

To increase quality of care, the quality of life of chronically ill patients, and to sustain healthcare costs, there is a large focus on enhancing self-management in people with chronic diseases in current guidelines and standards of care [4-6]. These guidelines are often based on the chronic care model of Wagner *et al*., a framework for integrated, patient-centered care [7]. The Department of Health of the United Kingdom defined self-management as ‘the care taken by individuals towards their own health and well being: it comprises the actions they take to lead a healthy lifestyle; to meet their social, emotional and psychological needs; to care for their long-term condition; and to prevent further illness or accidents’ [8]. Following this definition, self-management also means that the patient takes more responsibility for his or her own health.

Self-management programs have been developed for various chronic diseases and lifestyle changes [9-12]. Several studies have shown positive effects of these programs on clinical outcome measures, as well as patient-related outcome measures, such as participation, knowledge or activation [13-18]. These studies identified several factors that influence the probability of successfully completing the intervention, such as social support or self-efficacy.

In other fields of research, especially human genetics, the concept of personalized medicine has been introduced [19]. In the field of genetics, patients are genetically screened, and subsequently receive treatment that is adapted to their genomic profile. In psychology, treatment is adjusted to psychological characteristics and thus, person-centered [20-22]. We applied the concept of personalization to self-management support. Here, personalization is defined as adjusting the self-management support to the individual characteristics of the patient. For example, in the case of low self-efficacy, the practice nurse and patient make an individual care plan with small steps in goal setting to enhance the self-efficacy of the patient. Current generic self-management measures include the patient activation measure (PAM-13), which measures the current level of self-management and the Health Education Impact Questionnaire (heiQ), measuring the outcome of an intervention or education program [23,24]. However, there was no generic instrument available to identify factors that could hinder successful self-management. For this purpose, we developed a self-management screening questionnaire (SeMaS), as described below. Providing patients with personalized self-management support, we expect the patient-activation level to increase, which subsequently has a positive effect on health-related lifestyles, knowledge, skills, and the ability to take care of the chronic condition. This in turn will positively influence overall health and wellbeing. The SeMaS questionnaire will provide specific information about the abilities and possible barriers for self-management. Using a manual, the healthcare provider will have a starting point to influence possible barriers and stimulate self-management. This is shown in the logic model in Figure 1.

**Figure 1 F1:**
[figure not shown]
Logic model of the hypothesized effects of self-management screening questionnaire (SeMaS).

The main research objective is to assess the effectiveness of the SeMaS questionnaire and subsequent personalized self-management support on patients’ self-management behaviors.

## Methods/Design

We will conduct a two-arm practice-level randomized trial with a postponed intervention in the control arm. The practice nurses will be trained in the SeMaS method. Since practice nurses were trained in the SeMaS method, the intervention was implemented at general practice level instead of patient level. Another problem in this study was the risk of contamination when control patients would be exposed to elements of the intervention. Therefore, randomizing all patients within a general practice (representing a cluster) to either the intervention or the control was the most logical choice.

### Practices

For this study, we recruited the practices through the primary care cooperation *De Ondernemende Huisarts* (DOH), or The Innovative General Practitioner. DOH is an innovative organization led by GPs who have a subspecialization. The care group comprises 15 general practices in the southeast part of the Netherlands, varying in size and degree of urbanization. Half of the practices are situated in the city, while the other half are located in surrounding villages. The context of this care group provided a well-developed infrastructure to perform this study. Together the practices serve approximately 115,000 patients who are registered at the practice according to the Dutch capitation system. The practices are group practices, in which groups of GPs work together, and are supported by practice nurses (64 GPs and 54 nurses in total). These nurses usually perform planned checkups following treatment protocols, while the GPs perform the annual checkups for chronically ill patients.

DOH has formulated a policy agenda for self-management in chronic patients [25]. The cooperation offers several self-management interventions or types of self-management support that are evidence-based as far as possible. The program of interventions consists of group courses, including the course ‘Beyond good intentions’, and group courses for smoking cessation, and an exercise project, KICK, which guides patients to local sport unions via physiotherapists [18,26].

The eHealth interventions consist of the Diabetes Interactive Education Program (DIEP), an Internet decision-aid for smoking cessation, patient education via informative websites about asthma and chronic obstructive pulmonary disease (COPD) from the Lung Foundation Netherlands and exercise (30minutenbewegen.nl), and a patient portal with options for self-monitoring and digital coaching on exercise, diet and smoking cessation [27].

The GPs and practice nurses have had training in motivational interviewing and the approach known as actual practice and maintenance, consisting of a behavior change model (referred to as a series of steps) and so-called person-related factors to enhance self-management [28,29]. Motivational interviewing is a client-centered counseling technique to facilitate and engage intrinsic motivation of the patients in order to change behavior. It has been found to be effective in several studies [30-32].

All 15 general practices of the DOH will participate in the trial. We recruited the practices through the DOH cooperation. The practice nurses will receive training in working with the SeMaS. As mentioned, we will perform randomization at the cluster level. Furthermore, as the ability of the practice nurse to influence the self-management behavior of the patient can affect the study results, we dichotomized practices into two equal groups using the percentage of practice nurses in the practice that participated in the behavioral change training [29]. Also, practices were dichotomized in two equal groups using the volume of practice nurses corrected for practice size, as the workload can affect the study results as well. This resulted in four strata. For each stratum, a separate two-block randomization list was produced to randomize the practices to the control or intervention arm [33]. Two practices were coupled in the randomization procedure to prevent contamination, because one practice nurse worked in both practices. The final allocation of practices is shown in Table 1.

**Table 1 T1:** Randomization strata and the number of practices per stratum of the SeMaS study

	**Low participation in behavioral change training**		**High participation in behavioral change training**	
	**Intervention**	**Control**	**Intervention**	**Control**
Low volume of practice nurses	2	1	2	2
High volume of practice nurses	1	3	2	2

Volume of practice nurses: the number of full time equivalents divided by the number of patients in the practice. Participation in training: percentage of the practice nurses who attended the training for behavioral change to enhance self-management that was provided in 2011 [29]. SeMaS, self-management screening questionnaire.

A representative of the care group DOH consented with participation in the study for all practices. After performing the randomization procedure, we informed the practices about participation in the study.

### Patients

The population of chronically ill patients in the practices consists of approximately 9,100 patients with cardiovascular risk, 3,900 diabetes mellitus patients, 1,500 asthma patients and 900 COPD patients. These patients are regularly seen by the practice nurse. Patients can be included if they are over 18 years of age, have at least one of these chronic conditions and have a checkup appointment with the practice nurse in the inclusion period. Practices will send invitations with information about the study and informed consent forms to patients to participate in the study approximately 4 weeks before the planned checkup appointment of the patient. Patients will be given the option to fill in the questionnaires either digitally through the Internet or on paper. Participating patients will be asked to fill in an evaluative questionnaire one week after their consultation, and the final questionnaire after 6 months.

Medical-record data extraction will be performed by the data management agency of the care group. They can provide anonymous data on the participating patients from the research period. The research team will perform medical-record data analysis. The flow chart of the trial is shown in Figure 2.

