### Sample size

Sample size calculations have been made using the results from three studies on the primary outcome measure, PAM-13 [17,34,39]. In these studies, improvements in PAM scores after intervention vary from 4% to 8% (SD 12 to 17). Based on these studies, we expect to find a difference in PAM score of 6% (SD 14.0) in this study. For the power calculations, we assume an intraclass correlation coefficient (ICC) of 0.05 based on the article of Campbell *et al*. [40]. This article states that an ICC of 0.0 to 0.5 is normal for outcomes in primary care research. To reach a power of 80% and alpha of 0.05, and considering ICC of 0.05, at least 25 patients per practice are needed when using 15 practices. With an expected dropout rate of 33%, 33 patients would be needed per practice, thus, 495 in total. Our secondary outcomes comprise lifestyle measures that will not be applicable to every patient, such as smoking. Therefore, we strive to include 50 patients per practice. Thus, 750 patients will be included in total.

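### Practices that know their arm send the invitations, and the stated limits leave them able to influence which eligible patients enter the trial

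*Protocol article*

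**What the plan says.** All places are in the protocol article.

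- **Order of events** (Practices): "After performing the randomization procedure, we informed the practices about participation in the study".
- **Knowledge of arm**: intervention nurses and GPs are trained before the trial begins and receive a manual that sorts profiles by suitability for self-management (Training and support of practice nurses in the intervention arm). Control practices deliver usual care and are trained a year later (Self-management support).
- **Who recruits** (Patients): "Practices will send invitations with information about the study and informed consent forms to patients to participate in the study", about four weeks ahead of a checkup.
- **Who is eligible** (Patients): "Patients can be included if they are over 18 years of age, have at least one of these chronic conditions and have a checkup appointment". It must be a nurse checkup that falls within the inclusion period, whose length is not given.
- **Alignment of the arms** (Self-management support): control patients are invited in the same period as intervention patients.
- **Target** (Sample size): "Therefore, we strive to include 50 patients per practice", and "Thus, 750 patients will be included in total".
- **Recruitment bias** (Limitations of this study): attributed to which patients respond. Privacy law rules out analysing the characteristics of non-responders.

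**The concern.** In a cluster trial, randomising practices balances the practices and their whole patient lists in expectation. It does not protect a patient sample that is assembled later by people who know the allocation. Intervention nurses know that they will work with the profile of each patient who joins; control nurses receive no profile. If this leads the two arms to approach different kinds of patient, the arms differ before any intervention is given.

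The primary analysis is a multilevel ANCOVA on follow-up PAM-13 with baseline PAM-13 as covariate. That corrects for an imbalance visible in the baseline score. It does not fully correct for a nurse's judgement of who is likely to change. Intention-to-treat applies only once a patient is enrolled, and the analyst blinding described for the secondary outcomes comes too late to affect entry. The three SeMaS readiness subgroups are exposed in the same way.

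**Working it through.** **1. The plan's own target.** The inputs from Sample size are a difference of 6, SD 14.0, power 80%, alpha 0.05 (taken as two-sided), ICC 0.05 and 15 practices.

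- Without clustering: 2 × (1.96 + 0.84)² × 14² / 6² gives 86 per arm after rounding up.
- Design effect at 25 per practice: 1 + 24 × 0.05 = 2.2.
- 86 × 2.2 = 189.2 per arm, and 2 × 189.2 / 25 = 15.1 practices. Power with 15 practices of 25 is 0.799.

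So "at least 25 patients per practice are needed when using 15 practices" reproduces. The next step, "33 patients would be needed per practice, thus, 495 in total", is 25 × 1.33 = 33.25, then 33 × 15 = 495. The working target is 50 × 15 = 750. The size of the trial is not in question here; 750 serves as the denominator below.

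**2. The pool.** Patients gives "9,100 patients with cardiovascular risk, 3,900 diabetes mellitus patients, 1,500 asthma patients and 900 COPD patients".

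- Sum: 9,100 + 3,900 + 1,500 + 900 = 15,400 condition counts, or 15,400 / 15 = 1,027 per practice.
- These are counts by condition, and a patient with two conditions may be counted twice. If every other patient also has cardiovascular risk, the smallest number of individuals is 9,100.
- Eligibility also needs a nurse checkup within the inclusion period. The share who have one is not stated; 10% to 100% is assumed.

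**3. Eligible patients per patient wanted** (pool × share / 750):

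| Share with a checkup in the period (assumed) | Pool 15,400 | Pool 9,100 |
|---|---|---|
| 100% | 20.5 | 12.1 |
| 10% | 2.1 | 1.2 |

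**4. Eligible patients per invitation needed.** Not everyone invited will consent. With an assumed response of 20% to 50%, 750 participants need 750 / 0.5 = 1,500 to 750 / 0.2 = 3,750 invitations.

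| Share with a checkup (assumed) | Pool 15,400 | Pool 9,100 |
|---|---|---|
| 100% | 4.1 to 10.3 | 2.4 to 6.1 |
| 10% | 0.4 to 1.0 | 0.2 to 0.6 |

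In the top row practices have room to select. In the bottom row they would have to invite everyone, and no room is left. The article says that these patients see the practice nurse regularly, which makes some surplus plausible but does not give its size.

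**5. The stated limits, taken in turn.** Eligibility defines the pool, not the order in which it is used. The four-week timing says when a patient's letter goes out, not whether every patient with an appointment gets one. The common inclusion period aligns the calendar between arms, not the choice of patient within it. The target of 50 says roughly where recruitment ends, not how it gets there. Together they are compatible with inviting everyone and also with inviting selectively.

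**The case against.** The strongest reply is that the text says only that practices send letters, triggered by an appointment. Inviting every patient with a checkup fits that equally well, and no sentence gives nurses discretion. This stands: that practices choose their invitees is something a reader might infer, but the article neither describes nor excludes it. The supported statement is that they can influence who is invited.

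A reader might also take the 15,400 as eligible patients and conclude that there are about 20 for each one needed. The document does not support that. The figure may count patients more than once, ignores the checkup criterion and is set against patients enrolled, not invited. Twenty-fold is a ceiling.

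A third inference is that selection would favour the intervention. The manual separates suitable from unsuitable profiles, which might draw nurses to ready patients. Yet much of the support it describes is for patients with barriers, such as low self-efficacy or low social support, and a nurse might as readily invite those. The direction is open.

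Finally, an article condenses the full protocol, which may hold an invitation rule. That is possible, and if it does, one sentence closes the point. But the article itself sets out the sequence, the inviter and the criteria, and discusses recruitment bias, and there it considers only how patients respond. What it states leaves this route open.

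**Conclusion.** The point holds as a weakness in how patients enter the trial: invitation follows open allocation, is carried out by staff who know their arm, and is bounded only by criteria that do not determine who is approached. It is not evidence that selective invitation has occurred.

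The surplus of eligible patients over 750 lies between about 1.2-fold and 20.5-fold, under the assumed 10% to 100% with a checkup in the period and an unknown overlap between conditions. Measured against invitations it may vanish.

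No size can be given for the bias in PAM-13. One could assume that favoured patients improve by 6 points more and are over-represented by 10 to 25 percentage points in one arm, which gives 0.10 × 6 = 0.6 to 0.25 × 6 = 1.5 points. Both inputs would be invented, the 6 merely repeats the planned effect, and the sum ignores the baseline adjustment, so it says nothing about this trial. The case for acting rests on two things: the safeguard is inexpensive, and non-responders' characteristics cannot be examined afterwards.

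**What to change.** For all invitations not yet sent, apply the same rule in both arms:

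- A standard query, run inside each practice's own system, lists every patient over 18 with one of the four conditions and a nurse checkup in the inclusion period. The care group's data agency is described only as supplying anonymous data on participants, so the list should not depend on it.
- Patients are invited consecutively by appointment date, or as a random sample of the list, until the practice target is met.
- A patient is removed from the list only for a logged reason.

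Report the numbers listed, removed, invited and consenting by arm. These are counts, so they do not require the non-responder characteristics that privacy law excludes. State how the patients already invited were chosen, since recruitment was under way at submission. Add selection at practice level after open allocation to Limitations of this study.

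The cost is one query per practice, a short log, an amendment and a little less freedom for practices in their mailings. The rule cannot repair invitations already sent; for those, disclosure is all that is available. If practices already invite every eligible patient, saying so and giving the counts is enough.

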**Figure 2 F2:**
[figure not shown]
**Flow chart of the self-management screening questionnaire (SeMaS) cluster randomized trial.** Baseline measurements and measurements at time (T) = 6 months include: SeMaS, Patient Activation Measure (PAM-13), perceived competence scale, short test of functional health literacy in adults (S-TOFHLA), rapid assessment of physical activity (RAPA), rapid eating assessment for participants-short (REAP-S), and smoking. DOH, *De Ondernemende Huisarts* (The Innovative General Practitioner).

### Ethical approval

The study has been reviewed by the local Medical Research Ethics Committee, the CMO region Arnhem-Nijmegen (registration number: 2012/561). The study will be carried out in accordance with the applicable rules concerning the review of research ethics committees and informed consent.

### Self-management screening tool: SeMaS

The SeMaS questionnaire was developed in four steps. First, we performed a broad, systematic literature search to identify reported aspects that are associated with successful or unsuccessful self-management. Second, we held focus groups with professionals from primary care (GPs, psychologist, dietitian, physiotherapist, pharmacist) and patients to identify the most important aspects that would determine the chance of successful self-management, based on their experience and the literature search. The final selection of aspects was made in the stakeholders group, combining the findings of the literature study and focus groups. The aspects were selected if they were mentioned in the focus group, found in the literature, and an instrument was available. Third, we developed a prototype of the SeMaS and tested it in 24 consultations for applicability and readability, resulting in minor adjustments. Fourth, we validated the SeMaS in a test with 200 patients. Patients completed the SeMaS before their control visit with a practice nurse. After two months, patients completed a second questionnaire with SeMaS, reference questionnaires, and an additional questionnaire for process evaluation. Also, medical record data was extracted for process evaluation. Specifically, data were collected on referrals to self-management interventions, and advice or instructions provided to enhance self-management. Analysis of the data resulted in minor adjustments of the SeMaS.

SeMaS is designed to be generally applicable to patients with chronic conditions. It consists of 27 items divided over the relevant aspects of self-management, namely, burden of disease, locus of control, self-efficacy, social support, coping style, anxiety, depression and skills (computer, groups and self-care). A publication of the validation study of SeMaS is in progress.

Screening with SeMaS results in a personal profile on these aspects that are important for self-management, divided into three categories per aspect: 1) capable of (more) self-management, 2) capable of self-management with minor barriers, and 3) major barrier(s) for (more) self-management at this time. These categories were based on the scoring categories of the original instruments, and face validity. SeMaS will support the creation of individual care plans, make it possible to influence barriers for self-management, and support the referral to and participation in self-management activities. The profile will provide an overview of the aspects needing special attention when undertaking self-management activities.

